## Abstract

**Background:**

Identifying critical life transitions in people’s physical activity behaviors may illuminate the most opportune intervention apertures for chronic disease prevention. A substantive evidence base now indicates that parenthood is one of these critical transition points for physical activity decline. This study will examine whether a brief theory-based intervention can prevent a decline in physical activity among new parents over 6 months following intervention. This study protocol represents the first dyad-based physical activity initiative in the parenthood literature involving both mothers and fathers; prior research has focused on only mothers or only fathers (albeit limited), and has shown only short-term changes in physical activity.

This study will be investigating whether a theory-based physical activity intervention can maintain or improve moderate to vigorous intensity physical activity measured via accelerometry of new parents over a 6 month period following intervention compared to a control group.

**Methods:**

This study is a 6-month longitudinal randomized controlled trial. Parents are measured at baseline (2 months postpartum) with two assessment points at 6 weeks (3.5 months postpartum) and 3 months (5 months postpartum) and a final follow-up assessment at 6 months (8 months postpartum). The content of the theory-based intervention was derived from the results of our prior longitudinal trial of new parents using an adapted theory of planned behavior framework to predict changes in physical activity.

**Results:**

A total of 152 couples have been recruited to date. Sixteen couples dropped out after baseline and a total of 88 couples have completed their 6-month measures.

**Discussion:**

If the intervention proves successful, couple-based physical activity promotion efforts among parents could be a promising avenue to pursue to help mitigate the declines of physical activity levels during parenthood. These findings could inform public health materials and practitioners.

**Trial registration:**

This trial has been registered with the Clinical Trials Registry maintained by the National Library of Medicine at the National Institutes of Health on April 19, 2014. The registration ID is NCT02290808.

**Electronic supplementary material:**

The online version of this article (10.1186/s12889-017-4874-7) contains supplementary material, which is available to authorized users.

## Background

There is convincing evidence that physical activity is associated with numerous health benefits and a reduced risk of chronic disease and premature mortality [51, 69]. In addition to the physical health benefits obtained by physical activity, there are also numerous mental health benefits. These include improvements in well-being, reduction of depression and anxiety, enhancements of cognitive functioning and improvements in overall quality of life [8, 24, 45]. Despite the vast number of benefits associated with regular physical activity, the majority of adults do not meet the recommended guidelines of 150 min of moderate to vigorous activity accumulated over the course of a week [16]. Results from the Canadian Health Measures Survey showed that adults aged 18-79 yr. accumulated just 12 min per day of moderate-to-vigorous physical activity (MVPA) and that only about 1 in every 5 adults was actually achieving the recommendations [16].

There is also evidence to suggest that the onset of parenthood may contribute to a decline in physical activity for adults [7, 29, 54]. First-time parents in particular represent a population who could greatly benefit from the effects of physical activity due to parenthood being associated with decreased sleep, increased stress, anxiety and reduced mental well-being [19, 20, 40]. Thus, parents of young children may be an important population to target given the evident decline in physical activity and important roles they play with regard to their children’s physical activity. Eighty-five percent of Canadians will become parents during their lifetime and the mean age for first-time parents in Canada is 28.5 yr. [61]. The additional demands of parenthood necessitate lifestyle changes and this may compromise the personal physical activity behaviors of new parents [7, 12]. Indeed, in a recent review examining longitudinal physical activity studies parenthood emerged as a significant predictor of physical activity decline [54]. In a trial examining physical activity trends across non-parents, first-time parents and second time parents, up to 50% of adults who were regularly active drop their physical activity behaviors when they become parents and this deficit is still present after 5 years [48]. The effect was shown in both fathers and mothers, suggesting that both parents experience these declines in their physical activity behaviors, although women appear to have a steeper trajectory in MVPA decline. A study by Mailey and McAuley [34] noted that mothers have the lowest physical activity self-efficacy (i.e., perceived confidence to be active) of any group they have examined, including frail elderly and diseased populations. Clearly, parents represent an important physical activity promotion demographic.

However, there has been limited research on the effectiveness of physical activity interventions targeting parents together. The majority of studies examined the impact of parents’ physical activity on their children’s’ physical activity [6], or is focused solely on the physical activity of mothers [23], with a few studies focusing on the physical activity of fathers [39]. In a review on physical activity interventions for post-natal mothers [23], 20 intervention studies were identified that had a physical activity promotion component among mothers between 4 and 12 weeks after giving birth. Out of the seven studies that focused specifically on improving physical activity among inactive moms, six had significant effects on MVPA. In the meta-analysis portion of the review, a moderate effect was found for an increase in frequency of physical activity at post-test suggesting that interventions to improve physical activity among post-natal populations can be an efficacious avenue for physical activity promotion efforts. Still, no research has examined whether intervening on physical activity in dual parent households has promise.

Despite the limited research targeting parents together to improve their physical activity, evidence from other health domains that have intervened at the couple level have shown some promise [3, 35]. For example, in a recent review evaluating couple-based interventions, four out of seven were found to be more effective than regular care [3]. From the literature that has focused on populations with chronic conditions, couple-based interventions have been found to be more effective than individual focused interventions [35]. Furthermore, there is evidence to suggest that couples change their physical activity behavior in tandem [48], and therefore targeting the couple could provide an effective mode for intervention to help mitigate the decline in physical activity during early parenthood.

### Theoretical framework

Understanding physical activity during parenthood has typically taken a social cognitive approach, where attitudes/outcome expectations, perceived norms and perceptions of capability (perceived control/self-efficacy) are considered the antecedents of intention and intention is the key causal agent in behavior [53]. The most popular applications have included social cognitive theory [5], theory of planned behavior [1] and the transtheoretical model of behavior change [41]. Overall, the evidence has not been supportive of attitude or normative changes that can predict physical activity decline in parents with the exception of some associations between affective aspects (e.g., stress relief) and physical activity [37]. By contrast, a sense of lowered capability – often from increased child care duties and the struggle to balance occupational and domestic responsibilities – has been a reliable predictor of physical inactivity in reviews of parenthood and physical activity research [7, 53]. Self-regulatory constructs (goal setting, planning, self-monitoring) have also shown evidence as explanatory mediating mechanisms within successful interventions in new mothers [23]. From a conceptual standpoint, self-regulatory constructs are often viewed as bridge constructs between good intentions and behavior [13, 27, 46, 58] and may be useful to augment traditional social cognitive approaches such as theory of planned behavior. The blend of evidence on motivational aspects such as perceived capability and self-regulatory constructs such as planning and self-monitoring form the theoretical basis for this trial.

### Pilot research

This research builds on prior longitudinal assessments of parenthood and health behaviors [49] as well as our prior randomized controlled trial examining self-regulator strategies and physical activity among parents [52].

Our prior research has shown that couples change their physical activity behavior and motivation together and therefore our intervention targets the couple. Indeed, changes at the level of the couple showed correlations between slopes and intercepts of *r* = .62 for behavior, and *r* = .39 to *r* = .71 [48, 49] for motivational constructs which demonstrates considerable symmetry in physical activity between mothers and fathers. Current approaches that target mothers may not be as effective at sustaining changes in physical activity as including both parents. Working with both parents allows for workload negotiation, social support and collective goals to be managed together. Although we have not located any published couple-based physical activity interventions for new parents to date there is evidence in other health domains/populations that couple-based interventions are more successful than individual-level interventions [9–11]. This study examines whether a couple-based physical activity intervention helps to maintain or improve physical activity among new parents.

### Objectives

The primary research question is whether a theory-based condition (based on an adapted theory of planned behavior) can maintain or improve adherence to regular moderate/vigorous intensity physical activity among new parents when compared to those in the control condition at 6 months post intervention (8 months after the birth of their first child). We also will explore four secondary research questions including:Does the theory-based condition improve motivational, health-related quality of life, and health-related fitness outcomes among new parents when compared to those in the control condition at 6 months post intervention?Can group differences among new parents with regard to these motivational, behavioral, and health-related fitness outcomes be explained through a mediation model?Can motivational variables predict adherence?Is there a seasonal, initial physical activity status, mental health or gender difference across primary outcomes by assigned condition?

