### Hypotheses

We hypothesize that physical activity will be higher for parents in the theory-based condition in comparison to parents in the control condition after controlling for possible confounds. The effect may wane over time from the initial measurement period at 2 months after the onset of parenthood but all outcomes will remain significantly higher 6 months after intervention. For the secondary research questions we hypothesize that the theory-based condition will change salient underlying motives (theory of planned behavior constructs, self-regulation constructs) for physical activity because its basis is from the key results of our prior longitudinal trial of new parents [52] and past interventions among mothers [23]. Health-related physical fitness and quality of life will also be higher for this condition in comparison to the control condition. All outcomes will remain significantly higher at 6 months post-intervention in the theory-based condition compared to the standard physical activity education group. Improvements in both groups of mothers may occur due to recovery from pregnancy, but our hypotheses should still hold. The covariance of the assigned conditions (theory-based, standard) on adherence will be explained by changes in the salient underlying motives for physical activity (i.e., manipulation check). In turn, the covariance between these salient underlying motives and health-related outcomes will be explained by physical activity adherence among conditions. The approach will test Ajzen’s [1] theory of planned behavior adapted to include self-regulatory constructs as a bridge between good intentions and behavior [46]. Affective attitude and perceived behavioral control will predict intention, intention will predict self-regulation constructs of planning and self-monitoring, and these will predict adherence across conditions. As for seasonal or gender differences we hypothesize that there will be no differences, however, this question is exploratory because there is limited research at present.

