### Trial design

This study is a two-arm, parallel design, single blinded randomized controlled trial (RCT). Participants (mothers and fathers) are randomized to one of two groups 1) physical activity theory-based condition; or 2) standard attention control condition for 6 months duration post parenthood onset (baseline assessment at 2 months postpartum and final follow-up at 8 months postpartum). The trial is registered with the National Library of Medicine at the National Institutes of Health and was registered on April 19, 2014. The registration ID is NCT02290808. We obtained ethical approval from the University of Victoria Human Research Ethics Board and all amendments to the study went through the Human Research Ethics Board.

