After the initial 6 week intervention period, couples are given online follow-up questionnaires sent via email to complete and accelerometers are dropped off to their house to be worn for another week and then are picked up by the research assistant. Contact is made initially with a phone call by the research assistant to setup a meeting time with participants and to prime them for the emailed online questionnaire. Both groups receive a site “booster” session on the same material but the intervention group focuses on revisiting their experiences over the past six-weeks and re-set goals and redefine/problem-solve obstacles. Participants in the control group receive a booster session but this is more of a general check in. The same protocol is followed at the 3 month time period. Thus, two booster sessions (six-weeks, 3 months) are provided to all participants. At 6 months follow-up (i.e., 8 months post-baby), parents are asked to return to the lab to complete a brief questionnaire, perform the final fitness test and participate in a brief end-of-trial quantitative questionnaire and qualitative interview to evaluate the impact of the intervention and usefulness of the intervention material. To gain a better understanding of the factors associated with physical activity we conduct semi-structured interviews with parents, in order to examine both *content fidelity* (“what is done”) and *process fidelity* (“how it is done”) related to the delivery of the intervention trial [18]. Although quantitative measurement of outcomes will enable us to examine the potency of our intervention, a process evaluation (whereby participants are interviewed) is also essential to examine the *extent to which the* program is delivered and implemented as planned.

To help study retention, we offer monetary compensation in the form of grocery store gift cards ($25 per participant, increasing by $5 each assessment) across the study.

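### The final visit is labelled six months post intervention, but on the article's own schedule it is six months after baseline and about three months after the last active booster

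*Protocol article*

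**What the plan says.** The interval is stated as time since intervention in several places. The Abstract (Background) says the trial asks whether the intervention can "prevent a decline in physical activity among new parents over 6 months following intervention", and its closing sentence repeats the interval. The Objectives put the primary question "at 6 months post intervention (8 months after the birth of their first child", and the first secondary question uses the same label. The Hypotheses say that "all outcomes will remain significantly higher 6 months after intervention" and, further on, that "All outcomes will remain significantly higher at 6 months post-intervention in the theory-based condition".

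The schedule is dated from birth. The Abstract (Methods) states: "Parents are measured at baseline (2 months postpartum) with two assessment points at 6 weeks (3.5 months postpartum) and 3 months (5 months postpartum", followed by "a final follow-up assessment at 6 months (8 months postpartum". Trial design agrees: "baseline assessment at 2 months postpartum and final follow-up at 8 months postpartum".

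On delivery, Procedures has couples randomised after the one-week baseline accelerometer wear, then describes an opening delivery period of six weeks, and then states: "Thus, two booster sessions (six-weeks, 3 months) are provided to all participants". Procedures and Intervention explain that in the intervention arm these in-person boosters return to benefits, goals, plans and problem solving. In the control arm the booster is closer to a general check-in.

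Musculoskeletal fitness treats the 6-month visit itself as the post-intervention point. Analysis strategy codes the linear trend as 0 at baseline and 1 at 6 months.

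**The concern.** A statement that an effect is still present a given time after an intervention depends on when the intervention ended. Here the label attached to the primary time point matches the time since baseline, while intervention content is still being delivered three months into that period. The boosters are more than neutral contact: they renew the self-regulatory components under test in one arm and not in the other, so the active contrast between arms is refreshed at 5 months postpartum.

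This matters because the Abstract sets the trial against earlier work that showed only short-term change, and the Hypotheses predict an effect that may wane yet stays significant at the stated distance from the intervention. A reader or evidence synthesis that takes the label at face value would record a longer post-intervention follow-up than the design provides.

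**Working it through.** **Inputs** (months postpartum, from Abstract, Methods, and Trial design): baseline 2; 6-week visit 3.5; 3-month visit 5; final visit 8. From Procedures: randomisation follows a one-week wear, delivery opens with a six-week period, and boosters fall at 6 weeks and 3 months. One week is taken as 7/30.4375 = 0.23 months.

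**Formula:** interval = final visit − anchor.

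**Reproducing the stated six months.** Anchor at baseline: 8 − 2 = 6.0 months. This is the only anchor that gives the stated figure, and it is not an intervention anchor.

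**Intervention anchors:**

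| Anchor | Calculation | Months to final visit |
|---|---|---|
| First session (no earlier than one week after baseline) | 8 − 2 − 0.23 | at most 5.77, about 5.8 |
| End of the opening six-week period, on the article's visit dates | 8 − 3.5 | 4.5 |
| The same, counted in days from the first session | 5.77 − 42/30.4375 = 5.77 − 1.38 | 4.39, about 4.4 |
| Last booster at the 3-month visit | 8 − 5 | 3.0 |
| Last booster, if held after that visit's one-week wear | 8 − 5 − 0.23 | 2.77, about 2.8 |

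**Reverse check.** A visit six months after the last booster would fall at 5 + 6 = 11 months postpartum. One six months after the opening delivery period would fall at 3.5 + 6 = 9.5 months. The article schedules neither. This only shows how far the label is from the schedule; it is not a proposal for another visit.

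**Consistency of the term.** If the 6-month visit is itself the post-intervention point, as in Musculoskeletal fitness, then no time has elapsed since intervention at that visit. That cannot stand beside the six months in Objectives and Hypotheses. The word is therefore used in two incompatible senses for one visit.

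**The case against.** The strongest reply is that nobody can mistake the visit. The sentence in Objectives gives the age of the child in parentheses, the Abstract (Methods), Trial design and Procedures all date the final visit to 8 months postpartum, and the model codes time from baseline. This stands: the visit and the primary model do not depend on the label. It does not rescue the label, because those dates are what show it to be wrong, and the Hypotheses and the Abstract (Background) carry no date beside the claim.

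A second reply is that the intervention is described as brief, with boosters named separately, so the term may loosely mean time since the first session. That gives at most about 5.8 months, which is close. But Procedures calls the six-week delivery period an initial one, the boosters renew the active content, and Musculoskeletal fitness uses the term in a way that does not fit this reading.

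Three stronger readings may tempt a reader, and the document supports none of them:

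- *That the article claims six months of persistence without contact.* No passage says so. The boosters are reported openly with dates and content, and the Discussion draws no such conclusion.
- *That maintenance should be judged only from 3 to 6 months.* In this article, maintaining or improving refers to physical activity measured from baseline, against the decline expected in new parents. It does not refer to an effect surviving withdrawal of the intervention. Restricting it would replace the primary question with another.
- *That the randomised comparison is compromised.* Booster sessions are scheduled at the same times in both arms, and nothing here shows bias or loss of power. Nor is it a fault that the 6-week and 3-month measurements fall within delivery, since the article presents them simply as assessment points.

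**Conclusion.** The point holds as an error of labelling and interpretation in the primary question, the first secondary question, the hypotheses and the abstract. The final visit is 6 months after baseline. Depending on the anchor, it is at most about 5.8, about 4.5 or about 3 months after intervention. The 3-month figure is the relevant one for persistence after delivery, and it is half the stated interval. It rests on counting the boosters as intervention, which their described content in the intervention arm supports. If only the opening six weeks are counted, the interval is still about 4.5 months. All figures assume visits fall on their nominal dates.

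The correction is worth making because it changes what may be concluded about persistence. It does not change the trial's design, data or primary test.

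**What to change.** - In the Abstract, Objectives and Hypotheses, replace the interval with *6 months after baseline (about 3 months after the last booster session)*.
- Align the Musculoskeletal fitness section, so that the 6-month visit is described the same way throughout.
- In the trial report, describe any persistence of effect after delivery ended as covering about 3 months.
- Keep the primary question as the baseline-to-6-month comparison with control, and leave the model as it is on this point.

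The cost is a few sentences and a slightly less favourable durability claim. No visit, measurement or sample size changes.

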### Hypotheses

We hypothesize that physical activity will be higher for parents in the theory-based condition in comparison to parents in the control condition after controlling for possible confounds. The effect may wane over time from the initial measurement period at 2 months after the onset of parenthood but all outcomes will remain significantly higher 6 months after intervention. For the secondary research questions we hypothesize that the theory-based condition will change salient underlying motives (theory of planned behavior constructs, self-regulation constructs) for physical activity because its basis is from the key results of our prior longitudinal trial of new parents [52] and past interventions among mothers [23]. Health-related physical fitness and quality of life will also be higher for this condition in comparison to the control condition. All outcomes will remain significantly higher at 6 months post-intervention in the theory-based condition compared to the standard physical activity education group. Improvements in both groups of mothers may occur due to recovery from pregnancy, but our hypotheses should still hold. The covariance of the assigned conditions (theory-based, standard) on adherence will be explained by changes in the salient underlying motives for physical activity (i.e., manipulation check). In turn, the covariance between these salient underlying motives and health-related outcomes will be explained by physical activity adherence among conditions. The approach will test Ajzen’s [1] theory of planned behavior adapted to include self-regulatory constructs as a bridge between good intentions and behavior [46]. Affective attitude and perceived behavioral control will predict intention, intention will predict self-regulation constructs of planning and self-monitoring, and these will predict adherence across conditions. As for seasonal or gender differences we hypothesize that there will be no differences, however, this question is exploratory because there is limited research at present.

